### Data collecting and monitoring

The governance of this study will be carried out by the trial steering committee (TSC), composed of the primary investigators and statisticians, who will oversee the entire study conduct to ensure that all researchers participating in this study are following the proposed protocol. A monthly meeting will be conducted where the TSC can supervise the progress and the data quality of this study and share suggestions if problems occur. The Ethics Committee will hold an annual meeting to monitor the implementation of the entire trial.

In this study, the data that includes observation time points, scanning time points, outcome measures, adverse events, and safety evaluations will be collected at baseline and weeks 4, 8, and 12 after the intervention using the case report form. And a special assistant will be responsible for reviewing data integrity, accuracy, and consistency. Patients will be assigned to a quiet room for psychological factor assessments. In order to ensure the consistency of source data, all the scales will be assessed by the same researcher during the study. Meanwhile, the research data will be input into EpiData electronic database. For ensuring the accuracy of data entry, data will be entered independently by two researchers, and then the discordances will be resolved by tracing source data.

When the trial is completed, the database will be locked by the data management team, after which the researchers can no longer modify the data. Both paper files and electronic documents will be preserved for at least 5 years after publication. If readers and reviewers have any questions, they can contact the corresponding author for access to the original data. Patient information will remain anonymous, including name, ID number, and telephone number.

### Statistical analysis

Before the data analyses, the research group will provide a statistical scheme to the statisticians. The scheme will include the required data and processing method. The data will be processed and analyzed by the statisticians by the scheme.

Intention-to-treat statistical analysis will be conducted. Missing data will be treated by imputation methods depending on the type: missing completely at random, missing at random, or not at random. Per-protocol analysis will include only patients who attended at least 80% of the sessions and completed the follow-up in the allocated intervention group.

Statistical analyses will be performed with SPSS 22.0 statistics software (IBM Corporation, Armonk, NY, USA). The data analysis process will be completed by statisticians who are independent of the research team and blinded to the test settings. A *t*-test and Wilcoxon test will be used to compare the numerical variables in the within-group analyses, including the WOMAC, VAS, AIMS2-SF, BAI, and BDI. Analysis of variance and the Kruskal-Wallis test will be used for numerical variables in the between-group analyses, including age, height, weight, scores of VAS, WOMAC, AIMS2-SF, BAI, BDI, and Credibility/Expectancy Questionnaire. The chi-squared test and one-way analysis of variance (ANOVA) will be used for categorical variables such as the demographic and baseline characteristics. The available data of the four groups (group A, group B, group C, and group D) will be tested by bilateral tests and the confidence intervals are all 95% bilateral, with a *P* value less than 0.05 being statistically significant.

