## Methods and analysis

### Study design

This is a randomized controlled trial (RCT) that aims to compare the effect of MA, EA, and WA acupuncture methods in the treatment of KOA. This trial has been approved by the ethical committees of the First Affiliated Hospital of Henan University of Traditional Chinese Medicine (No: 2021HL-158) and registered in the Chinese Clinical Trial Registry, ChiCTR2100049526. The protocol will be reported following Standard Protocol Items: Recommendations for Interventional Trials (SPIRIT) reporting guidelines [18] (Additional file 1). A total of 200 patients diagnosed with KOA according to the American College of Rheumatology clinical criteria will be recruited [19]. After informed consent acquisition, all patients will be randomly assigned to group A (MA group), group B (EA group), group C (WA group), and group D (SA group) based on the ratio of 1:1:1:1, to receive treatment. The treatment procedure will include 20 sessions of treatments in total from baseline to week 4 and 2 times of follow-ups on week 8 and week 12 respectively. Outcome measurements will be assessed according to the following time schedule. Figure 1 shows the study design in the flowchart, and Table 1 illustrates the time schedule of enrolment, interventions, assessments, and visits of participants.

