### Discontinuation criteria and modification

During the trial period, patients with KOA who meet the following criteria will be excluded from the study: (1) protocol violation such as taking analgesic without permission or receiving additional treatment that may interfere with the efficacy of acupuncture, (2) withdrawal of consent for study participation because the patients do not wish to continue, (3) missing more than 4 of 20 acupuncture treatment sessions, and (4) occurrence of a serious adverse event that the doctors consider should lead to termination of trial participation.

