#### Primary outcome

We will use the Western Ontario and McMaster Universities Osteoarthritis Index (WOMAC) [22] as the primary outcome measure. The WOMAC is a valid and reliable self-administered questionnaire that has been used widely in a variety of clinical trials involving patients with KOA. It can be used as an initial assessment of the intensity of pain and functional disability of KOA. The Chinese version of WOMAC consists of 24 items assessing the patients with KOA pain (5 items), stiffness (2 items), and physical function (17 items). Therefore, it can multidimensionally measure pain, stiffness, and physical functional disability [23]. All 24 questions will be listed on a numerical rating scale ranging from 0 (no symptoms) to 4 (maximum symptoms). Doctors need to help patients perform the self-assessment, collect the total score from the 24 questions, and record it. Higher scores indicate more severe symptoms or physical disability. The evaluation will be performed at baseline and weeks 4, 8, and 12 respectively after randomization; then, we will select the evaluation at week 4 as the primary outcome.

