#### Secondary outcome

① We will use the Western Ontario and McMaster Universities Osteoarthritis Index (WOMAC) evaluation at weeks 8 and 12 as the secondary outcome measure.② The pain visual analog scale (VAS) [24]: The VAS is an internationally recognized 10-point scale selected to quantitatively evaluate the level of knee pain during the study. It scores from “0 (none),” “about 2 (mild),” “around 5 (moderate),” “almost 8 (severe),” and “nearly 10 (unbearable)” spaced along the continuum. During the experiment, the VAS assessments will be performed at baseline and weeks 4, 8, and 12 respectively by independent assessors who are not involved in acupuncture treatments (asking subjects to indicate the pain intensity at the most painful points during walking and ascending/descending a step and overall).③ Arthritis Quality of Life Measurement Scale Simplified Scale (AIMS2-SF) [25]: We will use the Chinese version of the Arthritis Quality of Life Measurement Scale Simplified Scale by the Fudan University School of Public Health to assess the quality of life. Because this experiment is aimed at KOA patients, 5 items involving hands and arms in the physical dimension of this scale will be removed, and only the remaining 21 items will be used. All items are scored on a scale of 1 to 5, with the total score represented by the sum of 5 dimensions. The higher the score, the better the quality of life. The evaluation will be performed at baseline at weeks 4, 8, and 12 respectively after randomization.④Credibility/Expectancy Questionnaire: The Credibility/Expectancy Questionnaire is a quick and easy-to-administer scale for measuring treatment expectancy and rationale credibility for use in clinical outcome studies [26]. Participants will be asked “How much do you feel acupuncture therapy will help to reduce your symptoms?” at baseline.⑤ Emotional monitoring: Mood changes, such as depression and anxiety, are common concomitant symptoms of KOA. In order to monitor the impact of emotional changes on the condition of KOA, we will use the Beck Anxiety Inventory (BAI) [27] and Beck Depression Inventory (BDI) [28] to evaluate the emotional state of patients in this trial. The evaluation will be performed at baseline and weeks 4, 8, and 12 respectively after randomization.

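### Applied to the week-4 primary, the single per-protocol definition drops adherent patients with a valid week-4 WOMAC because they missed a week-8 or week-12 visit

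*Protocol article*

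**What the plan says.** The Statistical analysis section plans two analyses. The first is stated as "Intention-to-treat statistical analysis will be conducted", with imputation of missing data. The second has one definition and no variant by endpoint: "Per-protocol analysis will include only patients who attended at least 80% of the sessions and completed the follow-up in the allocated intervention group".

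The Study design section describes "20 sessions of treatments in total from baseline to week 4" and, as a separate item, "2 times of follow-ups on week 8 and week 12 respectively". Table 1 groups its columns the same way: week 4 is the last column under the treatment period, and weeks 8 and 12 stand under follow-up.

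Under Primary outcome, WOMAC is measured at baseline and weeks 4, 8 and 12, and "we will select the evaluation at week 4 as the primary outcome". Under Secondary outcome, the later WOMAC scores are secondary: "evaluation at weeks 8 and 12 as the secondary outcome measure".

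The discontinuation criteria have their own attendance limit, "missing more than 4 of 20 acupuncture treatment sessions". Missing a week-8 or week-12 visit is not among them.

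**The concern.** A per-protocol set for a week-4 endpoint should depend on what happened up to week 4: whether the patient received the allocated treatment and whether the endpoint was measured. By the Study design text, the 20 sessions are over by week 4. Attendance at week 8 or 12 therefore says nothing about adherence to those sessions and cannot change the week-4 score.

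The dependence can run the other way. A patient who is no better at week 4 may have less reason to come back, so the extra condition selects on an event that the endpoint itself can influence. The sample-size section expects success in 60% to 70% of the active arms and 40% of the sham arm, so loss related to outcome need not be equal across arms. If more sham non-responders drop out, the retained sham arm looks better than it was and the contrast with active treatment shrinks. A difference between the per-protocol and intention-to-treat results could then reflect attendance after treatment rather than adherence to it.

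**Working it through.** **1. What the rule does to a given patient.** Take a patient with 20 of 20 sessions, a week-4 WOMAC and no week-12 visit.
- Attendance: 20/20 = 100%, at or above 80%. Met.
- Discontinuation limit: more than 4 of 20 missed means fewer than 16 attended, that is below 16/20 = 80%. Not triggered. The two attendance thresholds agree, so the follow-up clause is a separate, additional exclusion.
- Follow-up completed: no. The patient is out of the per-protocol set, including for week 4.

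Reading follow-up loosely as all scheduled assessments gives the same result, because weeks 8 and 12 are still included. (Table 1 also marks the intervention rows under weeks 8 and 12, which does not agree with the Study design text. That needs reconciling in its own right. The step above uses only the 20-session count.)

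**2. The plan's own figure.** Sample size section: 45 per group, 10% loss. 45 / (1 − 0.10) = 50 per group, which reproduces the stated 50 (200 in total).

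**3. How many patients are affected.** Planned loss per arm is 50 × 0.10 = 5. Let f be the share of that loss falling after week 4 (not stated; an assumption). The rule removes 5f patients per arm who have a week-4 score:

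| f | per arm | four arms |
|---|---|---|
| 0 | 0 | 0 |
| 0.25 | 1.25 | 5 |
| 0.5 | 2.5 | 10 |
| 0.75 | 3.75 | 15 |
| 1 | 5 | 20 |

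This is before any exclusion for low attendance.

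**4. Bias if loss depends on outcome.** All of the following are assumptions: f = 1, week-4 improvement normal with SD 1 in each arm, and log-odds of loss falling by 1.0 for each SD of improvement. The retained mean is ∫ y(1 − p(y))φ(y − μ)dy / ∫ (1 − p(y))φ(y − μ)dy, with logit p(y) = a − y and a set to give the required loss.

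- *Dependence in one arm only, 10% loss:* that arm's mean shifts by 0.091 SD.
- *Same dependence in all four arms, average loss 10%:* arm means μ = Φ⁻¹(expected success rate), that is EA 0.524, WA 0.385, MA 0.253, SA −0.253.

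| Arm | Loss | Shift in retained mean (SD) | Sham shift minus arm shift (SD) |
|---|---|---|---|
| EA | 7.6% | 0.070 | 0.056 |
| WA | 8.6% | 0.078 | 0.048 |
| MA | 9.6% | 0.087 | 0.040 |
| SA | 14.3% | 0.127 | – |

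The net bias is 0.04 to 0.06 SD, towards a smaller difference between sham and active. Against the contrasts implied by the same success rates (EA 0.524 + 0.253 = 0.778 SD after rounding; MA 0.253 + 0.253 = 0.507 SD), that is 0.056/0.778 = 7% and 0.040/0.507 = 8%. In this scenario the loss is uneven: about 7 of 50 in sham (50 × 0.143) and about 4 of 50 in EA (50 × 0.076), averaging 5.

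- *Loss unrelated to outcome:* shift 0; only patients are lost.

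**5. Extreme case, for scale.** If exactly the worst 10% of one arm were removed and no other arm were affected, the shift would be φ(z₀.₁₀)/(1 − 0.10) = 0.1755/0.90 = 0.195 SD. At 20%, a rate the plan does not give, it would be 0.350 SD.

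**The case against.** The strongest reply is that this is one condensed sentence in an article. It does not say that the per-protocol analysis is applied to the week-4 primary, and it could describe a set of 12-week completers. A separate statistical scheme is promised to the statisticians, and set membership by visit could be settled there. A set of adherent completers is also a common simple definition.

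Part of this stands. Applying the rule to week 4 is a reading of a general sentence, though the natural one, since no endpoint is exempted. That the scheme could repair the rule does not answer the point. The article does not leave the definition open: it states an explicit rule, limited by the word only, and a scheme faithful to it would carry the problem forward.

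Three stronger conclusions are tempting and are not supported:
- *The primary result is biased or loses data.* The intention-to-treat analysis keeps every week-4 score; the defect is confined to the per-protocol analysis. Nor do the documents name that analysis as the formal check on the primary. They give it no stated role in the conclusion.
- *Five patients per arm will be lost this way.* Five is the upper end under evenly spread loss. The 10% allowance is not tied to weeks 8 or 12, and the number may be zero.
- *The bias is 0.19 to 0.35 SD.* That needs the worst patients to leave with certainty, from one arm alone, and the upper value needs 20% loss. The expected success rates leave 30% to 40% non-success in the active arms too, so the same mechanism would act there and partly cancel.

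**Conclusion.** The point holds in limited form. Followed as written, the per-protocol rule removes patients with at least 80% attendance and a valid week-4 WOMAC from a week-4 analysis because of visits missed after the endpoint, and nothing else in the article prevents this.

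The likely effect is small: 0 to 5 patients per arm under evenly spread 10% loss, and a net sham-versus-active bias of about 0.04 to 0.06 SD if all loss falls after week 4 and depends on outcome alike in every arm. It is about 0.09 SD if only one arm's loss depends on outcome, and zero if none does. The timing of loss and the strength of its link to outcome are assumptions, since the documents give neither. This is a cheap improvement of minor to moderate weight, not a threat to the primary analysis.

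**What to change.** Replace the single definition by one set per endpoint:
- Week-4 primary, and other week-4 outcomes: at least 80% of sessions (16 of 20) in the allocated group and the week-4 assessment (WOMAC for the primary), with no condition on weeks 8 or 12.
- Each week-8 or week-12 endpoint: the same attendance condition plus the assessment at that visit.

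The cost is a sentence or two in the Statistical analysis section. No new data are needed, and the intention-to-treat analysis does not change. The one drawback is that the per-protocol N will differ by visit and must be reported for each. The change should be made before the data are unblinded.

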### Patient and public involvement

Patients and the public were not involved in the development of this clinical trial protocol.

## Discussion

Acupuncture, as a complementary and alternative therapy, is widely used in patients with KOA with the advantages of high safety and fewer side effects, and it becomes increasingly accepted in the world. There is also a growing number of scholars studying on acupuncture for KOA, especially since 2015 when the number of studies has risen sharply [29]. These studies include traditional MA, EA, acupuncture on sensitive acupoints, and thread embedding acupuncture, which fully prove the effectiveness of acupuncture in the treatment of KOA [30–32]. In addition, some scholars have found that the 3 sessions per week of acupuncture work better in improving knee pain and dysfunction than 1 session per week of acupuncture and the benefit of 3 sessions per week persists throughout follow-up [33]. However, the acupuncture treatment method for KOA is still a research topic, particularly the difference in the efficacy of different acupuncture treatments for KOA needs further study. So, this trial is designed as an RCT. The completion of this trial will provide detailed and accurate evidence of the efficacy and safety of MA, EA, and WA on KOA. The advantages of the trial design are shown in the following aspects.

### Choose three classic acupuncture treatments for comparison

The efficacy of acupuncture in the treatment of KOA has been widely recognized internationally. Many organizations, including the Scottish Intercollegiate Guidelines Network [34] and the American College of Rheumatology [14], recommend using acupuncture to treat KOA. Since the invention of the electric acupuncture apparatus, some researchers have also studied the effect of EA on KOA and some studies have shown that EA seems to be better than MA for KOA, but the evidence does not seem to be sufficient [35]. Thus, EA may have a stronger impact on pain and function requires needs to be further confirmed by randomized controlled trials. WA is a characteristic Chinese medicine therapy widely used in clinical practice, which is a kind of therapy combining the advantages of acupuncture and moxibustion. According to the theory of Traditional Chinese Medicine, WA has the efficacy of warming and dredging meridians, regulating blood circulation, and relieving pain [36]. However, to the best of our knowledge, there is no critical appraisal of the evidence for WA in the treatment of KOA. In summary, MA, EA, and WA are all effective at treating pain and dysfunction in patients with KOA. However, few studies directly compare the effects of MA, EA, and WA on KOA. Therefore, this study creatively chooses MA, EA, and WA for comparison.

### Choose appropriate outcome assessments

The Western Ontario and McMaster Universities Osteoarthritis Index (WOMAC) is a valid and reliable self-administered questionnaire that has been used widely in a variety of clinical trials involving patients with KOA. It can be used as an initial assessment of the intensity of pain and functional disability of KOA. The survey shows that WOMAC has high reliability and is relatively simple in evaluating the joint function, pain, and stiffness of KOA patients. It is currently the most popular KOA functional assessment scale in clinical practice. The pain visual analog scale (VAS) is an internationally recognized 10-point scale selected to quantitatively evaluate the level of knee pain during the study. In the clinical evaluation of KOA, VAS is often used in conjunction with WOMAC, and this method is simple and easy and relatively objective and sensitive, as well as the results are intuitive and clear. Arthritis Quality of Life Measurement Scale Simplified Scale (AIMS2-SF) is a scale for measuring the quality of life of KOA patients. The questions in the AIMS2-SF are simple and clear. Patients only need to answer according to the actual situation. The reading level of elementary school or above can be completed by themselves, which is easy to accept for middle-aged and elderly KOA patients. In addition, the test-retest reliability of AIMS2-SF is generally satisfactory and items within the same dimension have high internal consistency. Compared with WOMAC, AIMS2-SF pays more attention to the overall quality of life of KOA patients, so it is widely used to determine the quality of life of KOA patients. KOA is a chronic disease that tends to occur in middle-aged and elderly people. The Credibility/Expectancy Questionnaire is a quick and easy-to-administer scale for measuring treatment expectancy and rationale credibility for use in clinical outcome studies. Due to long-term pain, patients are often accompanied by mood disorders such as depression and anxiety. Therefore, we added the Beck Anxiety Inventory (BAI) and Beck Depression Inventory (BDI) to the outcome assessments to focus on the emotional disturbance of acupuncture treatment for KOA patients. BAI and BDI are simple clinical tools to analyze subjective anxiety and depression symptoms of subjects. They are characterized by concise project content, easy to understand, and easy to operate and analyze.

### Strict quality control

Determining strict control methods is the key to ensuring the methodological quality of RCT. To improve the result reliability of this study, we designed the quality control program from the following aspects: (1) Acupuncture manipulation: The acupuncturists who will participate in the trial have been registered with the Ministry of Health of the People’s Republic of China as Chinese medicine practitioners and have more than 6 years of clinical experience. To avoid the manipulation difference, two veteran acupuncturists, who should receive special and standardized training before the trial, will carry out all the treatment with the standard operating procedure. In addition, superfluous communication between acupuncturists and patients during acupuncture is forbidden. (2) Standardized acupuncture treatment program: The absence of standardized treatment protocol for acupuncture not only obstructs data reproducibility across the discipline but also results in the scientific nature and therapeutic effect of acupuncture not being fully confirmed [16, 17]. In order to make our research reproducible, consistent, and as rigorously scientific as possible, our acupuncture expert panel unanimously approved a standardized acupuncture treatment protocol, which will use fixed and classic acupuncture points (standardized acupuncture with four main points) in patients in the treatment group during every therapeutic session. (3) Multiple separation principle: in this study, all researchers will be trained to receive special training to well understand the design and process of the trial, the use of the CRF, and measurements of quality. What is more, people responsible for recruiting participants, outcome assessors, and statisticians in the trial will not know each other about the grouping of patients. (4) Reduce potential subjective bias: The subjective outcomes may bias the trial results; therefore, we will use the following methods to minimize potential bias: we will train patients so that all patients fully understand the meaning of each scale, and ensure that all patients have the same understanding of the scale without bias. In addition, the outcome assessors will operate independently, they will not be involved in the trial design and statistical analysis, and they are only responsible for explaining the content of the scale to the patients without any inducements. (5) Trial monitoring team: We will set up a trial monitoring team, composed of two supervisory data collectors, investigators, and analysts who do not know the random assignment protocol, and they will oversee the entire study conduct to ensure that all researchers participating in this study are following the proposed protocol. A monthly meeting will be conducted where the trial monitoring team can supervise the progress and the data quality of this study and share suggestions if problems occur.

We will analyze and compare the therapeutic effects of MA, EA, WA, and SA, which will provide not only evidence for different kinds of acupuncture treatments to relieve pain and improve physical function in KOA patients but also visualization reference for the clinical application of acupuncture for KOA management.

